**Loneliness**

The Three-Item Loneliness Scale (TILS; Hughes, Waite [33]) is a brief self-report measure of loneliness. The three items that compose this scale were selected from the R-UCLA Loneliness Scale (Russell et al., 1980) and include: ‘How often do you feel that you lack companionship?’ (relational connectedness); ‘How often do you feel left out?’ (collective connectedness); and ‘How often do you feel isolated from others?’ (general isolation). Response categories for the TILS are: ‘Hardly ever (1)’, ‘Some of the time (2)’, and ‘Often (3)’. Total scores are calculated by summing item scores, with higher scores indicating greater loneliness.

**Help-Seeking**

The General Help-Seeking Questionnaire (GHSQ; Wilson, Deane [34]) is used in the current trial to assess participants’ intentions to seek help for suicidal thoughts from a variety of sources. Respondents are invited to rate, on a six-point scale from ‘Not applicable (0)’, ‘Extremely unlikely (1)’ to ‘Extremely likely (5)’, the likelihood of seeking help from three professional sources (school or university counsellor, mental health professional, Doctor/GP), four informal sources (boyfriend/girlfriend, friends, parents, other relative/family members), three telephone/online sources (phone helpline, internet website, mobile app) or no one. An optional item, ‘I would seek help from another source not listed above,’ is also provided. Higher scores represent stronger intentions to seek help.

The adapted version of Client Service Receipt Inventory (CSRI; Beecham and Knapp [35]) is designed to collect information about use of healthcare and social care services over a retrospective period of the past six months. Respondents are asked to indicate whether they have used any services in the past six months due to mental health problems, including suicidal thoughts on a binary scale (‘Yes’/’No’). Services include: hospital services, mental health helpline, crisis support team, police/ambulance, contact with a range of mental health professionals (e.g., social worker, counsellor), self-help group, and other medically qualified doctor.

## 6.4. Risk factors and other measures

**Demographic Information**

At the baseline assessment, participants are asked to provide their age, gender identity, gender assigned at birth, sexual orientation, contact information (email and mobile number), the state and area they live in (i.e., metropolitan or rural/remote), language spoken at home, who they live with at home, current relationship status, the highest level of education completed, employment status, and whether they have ever experienced or been diagnosed with mental illness. Information related to their service use is also collected, such as whether they have ever seen a mental health professional for a mental health problem and use of health or wellbeing apps.

**Grit**

The Short Grit Scale (SGS; [36,37]) is an eight-item measure assessing perseverance and passion for pursuing long-term goals. Half of the items are worded positively (e.g., ‘I am diligent’) while the other half are worded negatively (e.g., ‘New ideas and projects sometimes distract me from previous ones’) and are thus reverse scored. Items are rated on a five-point scale, ranging from ‘Not like me at all (1)’ to ‘Very much like me (5)’, with total scale scores ranging from 8 to 40.

**Negative Life Events**

The Negative Life Events Scale for Students (NLESS; Buri, Cromett [38]) is designed to assess the experience of stressful life events among students. Respondents are asked to indicate whether or not they have experienced 25 negative life events (e.g., death of a family member, being arrested) in the past year and if yes, how stressful that event has been for them. In the adapted version of this measure, items are rated on a five-point scale, ranging from ‘Not stressful (1)’ to ‘Extremely stressful (5)’. Higher mean scores indicate higher negative impact on life.

**Expectation of Treatment Success**

Four items were created to measure participants’ confidence and readiness in using an app to reduce suicidal thoughts, as well as the perceived importance of reducing suicidal thoughts and participating in research to reduce suicide risk. Items on this scale include ‘I am confident that people could reduce their suicidal thoughts using an app’ and ‘I think that participating in a study that aims to reduce suicidal thoughts is an important thing to do’. These items are rated on a five-point scale (ranging from ‘Strongly disagree (1)’ to ‘Strongly agree (5)’). Other items include ‘Please rate the importance of reducing your suicidal thoughts over the next six months’ (ratings range from ‘Not important (0)’ to ‘Very important (5)’) and ‘Please rate your readiness to reduce your suicidal thoughts by using an app’ (ratings range from ‘Not ready (1)’ to ‘Completely ready (5)’). Due to the nature of these questions, this measure is administered only once during baseline assessment. Total scores indicate higher expectation of treatment success.

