## 1.3. Tertiary Aims

To examine the engagement with the smartphone application in each condition, assessed as uptake (no. downloads), adherence (no. modules completed) and acceptability among intervention condition participants.

To examine whether there is a dose-response relationship between engagement with the application and the primary outcome (suicidal ideation).

To assess whether the LifeBuoy app significantly reduces insomnia, rumination, suicide cognitions, distress tolerance, and help-seeking intentions and behaviours at post-intervention and three-month follow-up relative to control condition.

To examine whether loneliness, demographics, perseverance, negative events (i.e., such as COVID-19), and expectation of treatment success mediate the relationship between allocated condition and the primary outcome (suicidal ideation).

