## 4.4. Condition Allocation

After screening and registration is complete, participants will be asked to complete the baseline assessment – which is also delivered online, via the trial portal (website). Upon completion of the baseline survey, they will be automatedly randomised to a condition via an algorithm built into the Research Engine trial software. Subjects are not informed of which condition they have been allocated to. The two applications both have LifeBuoy in their title and look the same, only the content differs.

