## 5.2. LifeBuoy-C (control condition)

For our control condition we created a sham app, LifeBuoy-C, which is designed to match LifeBuoy on expectancy and time on task to control for digital placebo effects. Similar to the intervention app, the control app contains seven brief non-therapeutic education-based modules. The topics are peripherally related to mental health and wellbeing, including confidence, performance stress, the importance of having goals, and the value of being present. Each module takes two to three minutes to read through. The control does not contain the toolbox but includes the help button for safety management. Participants in the control group will be granted access to the intervention app after they complete the three-month follow-up assessment.

At the completion of the final assessment, participants in the control condition will receive an email letting them know they received the non-therapeutic app (Appendix G). The email explains what being in the control condition meant, and why it is important to have a control condition when trying to establish the efficacy of an intervention. Within this email, they will be offered the opportunity to download, and have access to, the Lifebuoy therapeutic app for 6 weeks. The link to the app download will be embedded in the email. This will be the only communication regarding the app download, no additional reminders will be sent. Participants will be able to download the app at any point during that 6 week period. If they attempt to download it after the 6 weeks they will receive the following email: “Oops, looks like the link to the LifeBuoy has expired as it’s been longer than 6 weeks. We’re really sorry about that. If you’re not feeling great, please speak to your GP or call a crisis help line, such as LifeLine [name] or the Suicide Call Back Service [name]”.

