**Table. Overview of Survey Schedule**

| Measure | **Outcome** | **Screening** | **Pre** | **Post** | **4-month** |
| --- | --- | --- | --- | --- | --- |
| Demographics | Demographics | - | X | - | - |
| SIDAS | Suicidal ideation | - | X | X | X |
| PHQ-9 | Depression, suicide attempt | - | X | X | X |
| GAD-7 | Anxiety | - | X | X | X |
| DQ-5 | Psychological Distress | - | X | X | X |
| SGS | Suicide Cognitions | - | X | X | X |
| RTQ-10 | Rumination | - | X | X | X |
| ISI | Insomnia | - | X | X | X |
| SWEMWBS | General mental wellbeing | - | X | X | X |
| DTS | Distress tolerance | - | X | X | X |
| TILS | Loneliness | - | X | X | X |
| GHSQ | Help-seeking intention | - | X | X | X |
| Modified-CSRI | Actual help- seeking | - | X | - | X |
| Modified-NLESS | Negative life events | - | X | - | - |
| SGS | Grit | - | X |  |  |
| Expectations of Success | Expectations of Success | - | X | - | - |
| Satisfaction with app | Satisfaction | - | - | X | - |

Participants in both conditions will be reimbursed for undertaking the post-intervention(T1) and 4-month post-intervention (T2) follow up surveys to reduce attrition at these timepoints. Participants will receive a $20 e-giftcards (from GiftPay; see <https://www.giftpay.com.au/business/egifts.aspx>.) at each of these two timepoints, providing a total reimbursement of $40 per participant if they undertake both surveys.

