# Statistical Analysis

Mixed models repeated measures analyses, with maximum likelihood estimation and an appropriate covariance structure, will be used to evaluate the efficacy of the Lifebuoy app relative to the control condition. The primary outcome is severity of suicidal ideation as assessed by the Suicidal Ideation Attributes Scale [SIDAS] over time (pre- test to post-test; pre-test to follow-up). The mixed models approach incorporates all available data, including participants with missing follow-up data points, under the missing- at-random assumption. Analyses will therefore accord with the intention-to-treat principle. This same approach will be used to examine reductions in secondary outcomes (depression (PHQ-9) anxiety (GAD-7) psychological distress (DQ-5) and wellbeing (SWEMWBS)) and tertiary outcomes (rumination (RTQ-10) insomnia (ISI) general mental wellbeing (SWEMWBS) help-seeking (GHSQ, CSRI)) over time.

Potential mechanisms of the symptom reduction will be measured by the changes in the levels of distress tolerance (DTS), loneliness (TILS) or suicide cognition (SGS). Negative life events (NLESS), grit (SGS) and questions about expectation of treatment success are included in the surveys as potential moderators. Participants’ current medications/interventions will be controlled for data analysis.

Descriptive statistics will be used to evaluate app engagement for participants in both conditions. Adherence will be indicated by the number of modules completed by participants. Participant module access and module completion will be automatically collected via the app. The mixed model approach will be used to determine whether adherence moderates the change in SIDAS scores over time in the intervention condition.

Acceptability of the LifeBuoy app will be examined through semi-structured interviews with a subset of participants and questionnaires in the survey. The interview data will be analysed using thematic analysis [40]. An inductive approach, independent of a theoretical confirmative method will be used to identify and group themes. The researchers will then refine the themes and determine the final coding framework. Discrepancies will be resolved by a third researcher to ensure reliability of the process.

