**Expectations of Success**

**We’d just like to ask you about your expectations of success of the app you’ll be trialling shortly – which is known as LifeBuoy.**

| **What the participant will see** | | **Drop down response options available** |
| --- | --- | --- |
| I am confident that people could reduce their suicidal thoughts using an app. | --- select ---- | Strongly agree  Agree  Neither agree nor disagree Disagree  Strongly disagree |
| I think that participating in a study that aims to reduce suicidal thoughts is an important thing to do. | --- select ---- | Strongly agree  Agree  Neither agree nor disagree Disagree  Strongly disagree |
| Please rate the importance of reducing your suicidal  thoughts over the next 6 months. | --- select ---- | Not important  Somewhat important Moderately important Important  Very important |
| Please rate your readiness to reduce your suicidal thoughts by using an app. | --- select ---- | Not ready  Moderately ready  Ready  Completely ready |

Thank you so much for completing this questionnaire, we greatly appreciate it.

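### Expectancy is measured only before randomisation, so it can be a moderator but can neither check that the sham matches LifeBuoy on expectancy nor mediate the effect of allocation

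*Protocol*

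**What the plan says.** **The design statement.** Protocol section 5.2 introduces LifeBuoy-C as a sham that is "designed to match LifeBuoy on expectancy and time on task to control for digital placebo effects".

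**The measure.** Section 6.4 (Expectation of Treatment Success) describes four purpose-made items and adds: "Due to the nature of these questions, this measure is administered only once during baseline assessment". The survey schedule in section 6.5 agrees. The row reads "Expectations of Success | Expectations of Success | - | X", with the mark in the pre-intervention column and dashes at post-intervention and follow-up. Appendix C introduces the items as being "about your expectations of success of the app" that the participant is about to trial.

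**The order of events.** Section 4.4: "Upon completion of the baseline survey, they will be automatedly randomised to a condition".

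**The planned uses.** Section 1.3 asks whether several variables, including "expectation of treatment success mediate the relationship between allocated condition and the primary outcome". Section 7 (Statistical Analysis) says that "questions about expectation of treatment success are included in the surveys as potential moderators".

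**What is collected after allocation.** Satisfaction is collected at post-intervention (schedule row: "Satisfaction with app | Satisfaction | - | - | X"). The app logs modules accessed, modules completed and time per module (section 6.4, Engagement/Treatment Adherence). Neither the schedule nor Appendix C lists an expectancy, credibility or allocation-guess item after randomisation.

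**The concern.** The protocol gives expectancy two roles that concern what happens after allocation. The sham is meant to equalise it between arms, and expectation is to be tested as a step between allocated condition and SIDAS. The only measurement is taken before anyone has been allocated or has seen either app.

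This matters because the primary outcome is self-reported. Participants are also told in advance that one of the two apps is non-therapeutic (Appendix A). If control participants came to expect less once they had used their app, part of a SIDAS difference could be a placebo response. The trial would have no direct measurement with which to show or largely exclude that explanation. A statistical analysis plan could not repair this, because it cannot analyse answers that were never collected.

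**Working it through.** **1. What a baseline comparison can show.** Let E0 be expectancy at baseline and E1 expectancy after first use. Randomisation follows E0, so the expected arm difference in E0 is zero whatever the sham does to E1.

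A simulation illustrates this. It used 5,000 trials per setting, 189 per arm at baseline, 132 per arm afterwards, and an assumed within-person correlation of 0.5. The sham deficits in E1 are also assumptions. The table gives the share of trials with p < 0.05 for the arm difference.

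| Assumed sham deficit in E1 | Baseline measure | Post-allocation measure |
|---|---|---|
| 0 SD | 5.2% | 5.2% |
| 0.5 SD | 5.3% | 98% |
| 1.0 SD | 5.1% | 100% |

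The baseline measure rejects at the nominal 5% in every row, so it has no power against a mismatch that arises after allocation.

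**2. Mediator or moderator.** A mediator must be affected by allocation. E0 is fixed before allocation, so the path from condition to E0 is zero by design and the mediation question in section 1.3 has no informative answer. A moderator should be measured before allocation. The role in section 7 therefore fits the timing; the role in section 1.3 does not.

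**3. Plan's own sample size, for the numbers that follow.** Section 8 gives d = 0.30, pre-post correlation 0.50, power 0.80, alpha 0.05 (two-sided assumed), 30% attrition and 189 per arm.
- Normal approximation with baseline adjustment: n = 2 × (1.96 + 0.8416)² × (1 − 0.50²) / 0.30² = 2 × 7.849 × 0.75 / 0.09 = 130.8, so 131 per arm. 131 / 0.70 = 187.1, so 188.
- The t-based version gives 132 per arm. 132 / 0.70 = 188.6, so 189.

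The stated figure is reproduced. 189 × 0.70 = 132.3 gives 132 completers per arm.

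**4. What one post-allocation measurement would give.** In SD units the standard error of the arm difference is √(2/n).
- 132 per arm: √(2/132) = 0.123. 95% CI half-width 1.96 × 0.123 = 0.24 SD. Difference detectable with 80% power (1.96 + 0.8416) × 0.123 = 0.34 SD.
- 189 per arm: half-width 0.20 SD, detectable difference 0.29 SD.

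The protocol gives no response rate for a mid-trial survey. The 132 carries over its 30% attrition figure, and 189 is the upper limit.

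**5. The time-on-task half of the statement.** Seven LifeBuoy modules at 3 to 7 minutes total 21 to 49 minutes (section 5.1). Seven sham modules at 2 to 3 minutes total 14 to 21 minutes (section 5.2). The nominal lengths differ, but time is logged, so this half can be checked from planned data. Only the expectancy half cannot.

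**The case against.** The strongest reply is that section 5.2 states a design intention and never offers the baseline items as a check on it, and that section 7 uses those items as moderators, for which baseline is the right time. That stands as far as section 7 goes. It does not cover section 1.3, which assigns the same construct a mediating role.

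A second reply is that relevant data after allocation do exist. This also stands. Satisfaction at post-intervention covers helpfulness and willingness to continue or recommend, and engagement is to be described in both conditions, so a sham abandoned early would leave a trace. But satisfaction is retrospective and mixed with actual benefit, and the acceptability aim in section 1.3 is limited to the intervention arm. These are proxies for expectancy.

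A third reply is that evidence of an actual mismatch is thin. The apps share a name and appearance (section 4.4), and a participant who sees only one app has no means of noticing that the toolbox is absent. That is fair: the documents do not show that a mismatch will occur.

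A fourth is that an expectancy item asked during treatment is also coloured by early benefit. It is, which is why it should be reported descriptively, early, and not used for adjustment.

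**Conclusion.** The point holds in a limited form. Measured once before randomisation, expectancy can be a moderator. It cannot show whether the two apps raised equal expectancy, and it cannot mediate the effect of allocation. This follows from the order of events in sections 4.4, 6.4 and 6.5 and needs no numerical assumption.

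A reader might infer more, and the documents do not support it:
- **That the trial's main claim cannot be tested.** The randomised comparison on SIDAS remains valid and the hypothesis in section 1.4 is testable as planned. Matching on expectancy appears in one clause of section 5.2. The gap concerns interpretation: content against expectancy as the source of a difference.
- **That there are no data at all on how the control performed.** Time, usage and satisfaction are collected, although indirectly for this purpose.
- **That some share of the planned d = 0.30 is placebo response.** Multiplying a detectable expectancy difference by an assumed correlation with SIDAS change would turn a detection threshold into a bias. The documents supply neither a plausible mismatch nor such a correlation, so no size is given here.

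This is a worthwhile improvement, not a defect in the primary analysis.

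**What to change.** 1. Repeat two Appendix C expectancy items, confidence that an app can reduce suicidal thoughts and readiness to use one for that purpose, reworded to refer to the app received. Ask them once after allocation, in both arms, as early after first use as existing contacts allow. One option is alongside the 3-week check in section 12.1, leaving that check itself unchanged.
2. Report the arm difference with its 95% CI descriptively beside the primary result (half-width about 0.24 SD if 132 per arm respond). Do not adjust the primary analysis for it.
3. In section 1.3, remove baseline expectancy from the mediation aim, so that it agrees with section 7 in calling it a moderator only.
4. In section 5.2, word expectancy matching as a design intention unless the new data support more.

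**Cost.** Two extra items and one descriptive comparison. Answers may partly reflect early benefit, so an arm difference would not by itself separate placebo response from efficacy. Asking about the app received may prompt some participants to guess their allocation. Items 3 and 4 are changes of wording only.

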**Satisfaction with the intervention**

Eighteen items were adapted from a previous study to assess participants’ satisfaction with the LifeBuoy app [39]. This measure consists of three parts. The first part contains seven statements related to the usability, readability, and helpfulness of the app, and the respondent’s intention to continue to use and recommend the app. Participants are asked to indicate whether they agree or disagree with each item. The second part of this measure comprises ten questions pertaining to potential difficulties in using the app (e.g., forgetting to use it, feeling worse after using it). Participants are asked to indicate whether they agree or disagree with each item. In the last part of this measure, they are asked to rate the overall helpfulness of the app on a five-point scale, ranging from “Extremely unhelpful (1)” to “Extremely helpful (5)”. Higher scores on each item indicating higher satisfaction with the app.

**Engagement/Treatment Adherence**

This will be measured by the number of modules accessed and completed by participants, and the time spent on each module. This data is automatically collected via the app.

## 6.5. Assessment schedule

Data will be collected at baseline (day 0), post-intervention (day 42), and 4-month follow-up (day 182).The Table below describes the timing of each measure. All survey questions/items are described in Appendix C.

**Table. Overview of Survey Schedule**

| Measure | **Outcome** | **Screening** | **Pre** | **Post** | **4-month** |
| --- | --- | --- | --- | --- | --- |
| Demographics | Demographics | - | X | - | - |
| SIDAS | Suicidal ideation | - | X | X | X |
| PHQ-9 | Depression, suicide attempt | - | X | X | X |
| GAD-7 | Anxiety | - | X | X | X |
| DQ-5 | Psychological Distress | - | X | X | X |
| SGS | Suicide Cognitions | - | X | X | X |
| RTQ-10 | Rumination | - | X | X | X |
| ISI | Insomnia | - | X | X | X |
| SWEMWBS | General mental wellbeing | - | X | X | X |
| DTS | Distress tolerance | - | X | X | X |
| TILS | Loneliness | - | X | X | X |
| GHSQ | Help-seeking intention | - | X | X | X |
| Modified-CSRI | Actual help- seeking | - | X | - | X |
| Modified-NLESS | Negative life events | - | X | - | - |
| SGS | Grit | - | X |  |  |
| Expectations of Success | Expectations of Success | - | X | - | - |
| Satisfaction with app | Satisfaction | - | - | X | - |

Participants in both conditions will be reimbursed for undertaking the post-intervention(T1) and 4-month post-intervention (T2) follow up surveys to reduce attrition at these timepoints. Participants will receive a $20 e-giftcards (from GiftPay; see <https://www.giftpay.com.au/business/egifts.aspx>.) at each of these two timepoints, providing a total reimbursement of $40 per participant if they undertake both surveys.

